## Abstract

**Background:**

The 12-lead electrocardiogram (ECG) is the gold standard for detecting patients who will benefit from emergent revascularization due to occlusive myocardial infarction (OMI). However, the pathophysiology of acute coronary syndromes (ACS) is dynamic, and nearly half of patients with OMI do not present with typical ST elevation or have dynamic ECG changes due to spontaneous recanalization before invasive coronary angiography (ICA). Recently, an ECG-based artificial intelligence (AI) model was developed using expert interpretation of OMI. However, its performance is limited to retrospective evaluation of ECGs recorded minutes to hours before ICA.

**Methods:**

The AI-ECG thrombolysis in myocardial infarction (TIMI) study is an investigator-initiated prospective multicenter registry planning to enroll over 700 consecutive patients with ACS undergoing ICA in 9 centers across Europe. For all participants, a standard 10-second 12-lead ECG will be recorded at the time of coronary angiography. The primary end point is the AI model’s ability to identify patients with an actively occluded (TIMI 0-1) culprit coronary artery at the time of invasive coronary angiography using only single-standard 12-lead ECGs. Standardized angiograms will be used as a reference standard.

**Conclusions:**

AI-ECG TIMI is the first prospective registry of consecutive patients with ACS with standard 12-lead ECGs recorded at the very moment of ICA. This study will help characterize ECG findings of abnormal myocardial perfusion due to acute active ischemia and prospectively validate an AI model’s ability to detect them.

The current classification of acute coronary syndrome (ACS) identifies patients who will benefit from emergent reperfusion therapy based on electrocardiographic (ECG) ST-segment elevation (ST elevation myocardial infarction [STEMI]).^1^ However, the majority of patients with ACS present without typical ST-elevation, and at least 25% of these patients have an acutely occluded culprit coronary artery (occlusion myocardial infarction [OMI]) at the time of invasive coronary angiography (ICA).^2^, ^3^, ^4^

The new 2023 ESC Clinical Practice Guidelines for Management of ACS, suggest a plethora of STEMI-equivalent ECG criteria (eg, de Winter, hyperacute T-waves, posterior STEMI, or modified Sgarbossa criteria for left bundle branch block).^5^ However, their recognition at the first point of patient contact is suboptimal, leading to delayed invasive management, which is associated with 2-fold higher short-term and long-term mortality.^2^^,^^3^^,^^6^ Growing evidence calls for a new paradigm, going beyond the individual features of the ECG, categorizing patients as either presenting acute OMI or non-OMI.^3^^,^^4^^,^^7^, ^8^, ^9^ Moreover, the pathophysiology of ACS due to thrombotic occlusive coronary stenosis is often dynamic and impacts the ECG appearance throughout the index hospitalization. One-third of occluded culprit lesions in patients with true STEMI recanalize before ICA.^10^^,^^11^ Thus, based on their ECG findings before ICA, patients with OMI could further be subclassified into actively occluded (STEMI equivalents) or partially reperfused (eg, Wellens syndrome).

Recently, an artificial intelligence (AI) model was developed using a cohort of 18,616 patients with suspected ACS and with ECG expert annotations and angiographic outcomes, demonstrating 2-fold higher sensitivity compared with standard ECG assessment for STEMI criteria in detecting OMI in a multicenter international validation cohort.^12^ Since the validation was retrospective with variable times to coronary angiography, the study could not confirm whether the patients had acute active coronary occlusion (culprit thrombolysis in myocardial infarction [TIMI] 0-1) at the time of the ECG recording. Moreover, the AI model detected a broad spectrum of patients with OMI without explicitly differentiating between patients with active occlusion at the time of ECG recording and those with spontaneous recanalization after recent active occlusion.

A new AI model in development, AI-ECG TIMI, aims to subclassify acute OMI based on the state of the culprit coronary artery at the time of recording the ECG into (1) actively occluded (TIMI 0-1) and (2) open/reperfused (TIMI 2-3). AI-ECG TIMI is developed using ECGs of patients with ACS and OMI adjudicated by expert ECG interpretation in the context of outcome data available.

This prospective multicenter registry will enroll more than 700 consecutive patients with ACS referred for ICA as clinically indicated. In the AI-ECG TIMI study, standard 12-lead ECGs recorded shortly before ICA will be correlated with culprit coronary vessel blood flow assessed by the TIMI grade flow. In this study, we aim to (1) validate a new version of the AI model differentiating between persistent coronary occlusion and reperfused culprit coronary artery; (2) correlate definitions of OMI based on routine angiographic and laboratory parameters to abnormal myocardial perfusion; (3) describe the prevalence of active OMI without typical ST elevation (STEMI equivalent) ECG patterns during known, angiographically proven, persistent occlusion.

## Materials and methods

### Study design

The AI-ECG TIMI study is an investigator-initiated prospective, multicenter registry of ACS patients undergoing ICA as clinically indicated. The study is registered at ClinicalTrials.gov (NCT06528821). A total of 709 patients with ACS will be enrolled at 9 investigational sites in Belgium, Italy, and Austria, with each site responsible for an equal enrolment target of around 80 patients (Central Illustration). An academic core laboratory will analyze electrocardiographic and angiographic data. End points will be evaluated by independent statistical analysis using prespecified contingency tables.

**Central Illustration fig1:**
[figure not shown]
The AI-ECG TIMI study is a multicenter prospective registry of patients with ACS undergoing standard 10-second 12-lead ECG monitoring shortly before invasive coronary angiography. This database will be used to evaluate an AI-powered ECG model detecting ACS assessed by abnormal culprit coronary blood flow (TIMI 0-1). ACS, acute coronary syndromes; AI, artificial intelligence; ECG, electrocardiogram; TIMI, thrombolysis in myocardial infarction.

### Screening and eligibility criteria

Adult patients presenting to the emergency department triage (walk-in, referral, or via emergency medical services) with a clinical suspicion of ACS undergoing 12-lead ECG screening will be considered for initial eligibility assessment. Consecutive patients with a working diagnosis of ACS (both STEMI and non-STEMI) admitted for ICA as per standard practice will be included in the study. Interventional cardiologists will enroll patients before the ICA procedure, ensuring all eligibility criteria are met. A full list of inclusion and exclusion criteria is available in Table 1.

**Table 1 tbl1:** Inclusion and exclusion criteria.

Inclusion criteria

Potential subjects must meet all of the following criteria to be eligible for inclusion in the study: • Age ≥ 18 y • Patients with acute coronary syndromes undergoing invasive coronary angiography as clinically indicated • Availability of a standard 12-lead electrocardiogram performed at invasive coronary angiogram before percutaneous coronary intervention (maximum within 15 min before vascular access)
Exclusion criteria

Potential subjects will be excluded if any of the following conditions apply: • Individuals presenting for a nonemergent (elective) cardiac catheterization • Individuals presenting with chronic coronary syndrome or stable angina symptoms • Individuals without symptoms suspicious for acute coronary syndromes • Individuals with contraindications for cardiac catheterization • Individuals participating in clinical investigations or trials that may interfere with the procedures or outcomes of this study

### Index procedures

For all included patients with ACS undergoing ICA, 10-second 12-lead ECGs with standard lead placement will be acquired at 3 standardized time points: T1, before ICA (within 15 minutes before skin puncture); T2, after termination of standard diagnostic angiography or percutaneous coronary interventions (PCIs); T3, 90 minutes after PCI. Diagnostic angiography will be performed based on standardized projections—left anterior descending coronary artery: right anterior oblique (RAO) 30° − cranial (CRA) 30° projection; left circumflex coronary artery: RAO 40° − caudal 30° projection; right coronary artery: left anterior oblique 30° − CRA 15° or RAO 30° − CRA 0° projections. Angiograms will be recorded at a minimum of 25 frames per second and for a duration sufficient to capture the filling of the venous coronary system and backflow of the contrast agent into the aorta. For all patients undergoing PCI, as indicated, an additional standardized angiogram of the culprit vessel(s) will be acquired after PCI. For patients without a culprit vessel requiring urgent revascularization, T2 and T3 time points will be skipped.

### Core laboratory analysis

Quantitative analysis of coronary angiograms will be performed by an independent core laboratory at the Sapienza University in Rome, Italy. QAngio XA 3D/QFR Software (Medis Medical Imaging) will be used to assess minimum lumen area, percent area stenosis, reference vessel areas, lesion length, TIMI frame count, TIMI myocardial perfusion grading myocardial blush grade, and quantitative flow ratio.^13^ The baseline SYNTAX score, the residual SYNTAX score, and the Δ SYNTAX score will be calculated.

### Study outcomes

The primary end point is the AI-ECG TIMI model’s ability to identify patients with an actively occluded (TIMI 0-1) culprit coronary artery using only single-standard 12-lead ECG recorded at the time of ICA (T1). The primary end point will assess the accuracy, sensitivity, specificity, positive and negative predictive values, and F1 score of the AI model. Secondary end points will include the evaluation of the AI-ECG TIMI model performance in subgroups, benchmark analysis, and patient-related end points (Table 2).

**Table 2 tbl2:** Secondary end points.

**AI-ECG TIMI model end points**
1. AI-ECG TIMI model performance across subgroups: (1) demographic, (2) risk factors and comorbidities, (c) electrocardiographic, and (4) culprit artery territory 2. Correlation of AI-ECG TIMI model’s raw numeric predictions (between 0 and 1) with myocardial perfusion grading after percutaneous coronary interventions
**Benchmark analysis end points**
1. Validation of expert ECG interpretation blinded to all clinical information: a. Accuracy, sensitivity, specificity, positive and negative predictive values of expert interpretation of active OMI, reperfused OMI, and entirety of OMI b. Interrater variability of expert interpretation of active OMI, reperfused OMI, and entirety of OMI. 2. Benchmark of machine-based ECG interpretation vs blinded expert ECG interpretation vs OMI AI-ECG model to detect OMI on pre-ICA ECGs
**Angiographic definition end points**
1. OMI definitions using routine angiographic and laboratory parameters will be correlated to abnormal myocardial perfusion using correlation coefficients: a. OMI defined as acute culprit with (1) TIMI <3; OR (2) TIMI 3 with vessel stenosis of >70% b. OMI defined as acute culprit with (1) TIMI <3; OR (2) TIMI 3 and very high peak troponin elevation (hs-cTnT ≥ 1000 ng/L, cTnI of > 10.0 ng/mL, or cTnT of > 1.0 ng/mL or hs-cTnI > 5000 ng/L) c. OMI defined as acute culprit with TIMI <3 d. OMI defined as acute culprit with TIMI 0-1 2. Prevalence of STEMI-equivalent ECG patterns and their correlation to TIMI flow grade at angiography
**Patient-related end points**
1. Percentage (%) of AI ruled-in patients (OMI AI-ECG Model–positive interpretation within 10 min of recording ECG) at admission invasively managed within 2 h stratified by presence of formal STEMI criteria 2. D2B times of AI ruled-in OMI without ST-elevation criteria (NSTEMI-OMI) with ECG scanned into PMcardio within 5 min of recording the initial ECG 3. Percentage (%) of OMI patients stratified by presence of formal STEMI millimeter criteria at admission 4. OMI patients stratified based on ECG expert-rated OMI state (active vs reperfused) at presentation and culprit coronary flow at angiography 5. NSTEMI-OMI stratified according to immediate (<2 h) vs SoC (>2 h) invasive management (median): (1) peak troponin (maximum rise before fall), (2) left ventricular ejection fraction at discharge, (3) length of hospital stay, (4) length of cardiac care unit or intensive care unit stay, and (5) presence of life-threatening arrhythmias

AI, artificial intelligence; cTnI, cardiac troponin I; cTnT, cTnT, cardiac troponin T test; ECG, electrocardiogram; hs, high-sensitivity; ICA, invasive coronary angiography; NSTEMI, non–ST-elevation myocardial infarction; OMI, occlusive myocardial infarction; STEMI, ST-elevation myocardial infarction; SoC, standard of care; TIMI, thrombolysis in myocardial infarction.

### Statistical analysis

#### Sample size and interim analysis

The study sample size was estimated based on ECG expert performance in detecting active OMI in 466 ECGs of patients with ACS undergoing ICA within 2 hours. The experts could detect active occlusion with 91.2% sensitivity and 53% specificity. However, the analysis likely underestimated specificity, as 52% (53 of 101) of the expert false positives were patients with true STEMI with a patent vessel (TIMI 3 flow) at coronary angiography. The prevalence of active occlusion (TIMI 0-1 flow) at coronary angiography in an all-comer ACS population undergoing ICA is estimated to be around 40%.

Drawing from the aforementioned assumptions, we estimate that a cohort of 709 consecutive patients with ACS would be sufficient to accurately evaluate an AI model detecting active coronary occlusion with a precision of 5% and a 95% 2-sided CI, assuming a dropout rate of 10%. Due to the probable underestimation of ECG expert specificity, an interim analysis will be performed after 200 successfully enrolled patients. In the interim analysis, ECG experts will review the presence of active coronary occlusion on all ECGs recorded at the time of coronary angiography for all successfully enrolled patients. The sensitivity and specificity of ECG experts detecting TIMI 0-1 will be recalculated, and the required sample size will be updated.

#### Primary and secondary end points

A contingency table will be created to assess the primary end point comparing the diagnostic performance of the AI-ECG TIMI on the 12-lead ECG recorded at ICA compared with the reference standard of angiographically measured abnormal coronary blood flow. For all evaluation metrics, 95% CIs will be estimated by 10,000 iterations of the bootstrap method.^14^ A *P* value of <.05 will be considered statistically significant. For secondary end points, forest plots will evaluate demographic, electrocardiographic, and culprit artery subgroup model performance. For each subgroup, *P* values will compare performance within a subgroup to the performance of the model on the overall patient population. Some subgroups may be combined depending on data availability.

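### In forest-plot subgroups with few occluded patients, the planned bootstrap intervals for sensitivity and NPV can shrink to zero width, and the sensitivity interval covers too little

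*Protocol article*

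**What the plan says.** The metrics are fixed under Study outcomes: "The primary end point will assess the accuracy, sensitivity, specificity, positive and negative predictive values, and F1 score of the AI model". All of these except F1 are simple proportions. The interval method is fixed under Statistical analysis, Primary and secondary end points: "For all evaluation metrics, 95% CIs will be estimated by 10,000 iterations of the bootstrap method". For the secondary end points, the same paragraph plans that "forest plots will evaluate demographic, electrocardiographic, and culprit artery subgroup model performance". Table 2 lists the subgroup families as demographic, risk factors and comorbidities, electrocardiographic, and culprit territory.

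The article does not say outright that the bootstrap sentence governs the forest plots. Its wording and its place under a heading that covers both sets of end points make that the natural reading. No bootstrap variant, subgroup size or minimum size is given. The only provision for sparse data is "Some subgroups may be combined depending on data availability".

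**The concern.** A non-parametric bootstrap can only reproduce outcomes that are in the sample. A subgroup with no missed occlusion contains no false negative to draw, so no resample contains one. Sensitivity and NPV are then 100% in all 10,000 resamples, and the interval runs from 100% to 100%. More iterations reduce Monte Carlo error only, and Monte Carlo error is not the problem.

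Just below 100% the distribution is discrete and skewed, and with few occluded patients the percentile limits sit too high. A forest plot could then show a sparse subgroup with no error bar at all, or with a bar that excludes a miss rate the data cannot exclude. For a test meant to find occluded arteries, that error favours the model.

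**Working it through.** **Inputs.** From Sample size and interim analysis: "The experts could detect active occlusion with 91.2% sensitivity and 53% specificity"; prevalence of active occlusion 40%; precision 5% with a two-sided 95% CI; dropout 10%. From Study design: N = 709. My assumptions: the percentile variant, subgroup sizes chosen for illustration, and true sensitivities of 0.85 and 0.95 around the expert figure.

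**Step 1: the plan's own figure.** The number needed for a precision d is 1.96² × p(1 − p)/d².
- Specificity: 1.96² × 0.53 × 0.47/0.05² = 382.8 non-occluded; /0.60 = 638; /0.90 = 709. This reproduces the stated total.
- Sensitivity: 1.96² × 0.912 × 0.088/0.05² = 123.3 occluded; /0.40 = 309; /0.90 = 344. Specificity therefore drives N.
- Evaluable cohort: 638, of whom 0.40 × 638 ≈ 255 are occluded and about 383 are not.

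**Step 2: which metrics collapse.** Take an assumed subgroup of 50: 20 occluded, all detected, and 16 of 30 non-occluded correctly classified. Resampling patients 10,000 times gives these 95% limits:
- sensitivity 1.00 to 1.00
- NPV 1.00 to 1.00
- specificity 0.35 to 0.71
- PPV 0.42 to 0.75
- accuracy 0.58 to 0.84
- F1 0.59 to 0.86

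Only sensitivity and NPV lose their width.

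**Step 3: coverage of the sensitivity interval.** With n occluded patients and x detected, the percentile limits (many resamples) are the 2.5% and 97.5% quantiles of Binomial(n, x/n), divided by n. Coverage is the sum of the Binomial(n, p) probabilities over those x whose limits contain p. The chance of a zero-width interval is pⁿ; for example 0.912¹⁰ = 39.8%.

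| Occluded n | Chance of n/n at 0.912 | Bootstrap coverage at 0.912 | Interval wholly above 0.912 | Wilson coverage at 0.912 | Bootstrap coverage at 0.85 | Bootstrap coverage at 0.95 |
|---|---|---|---|---|---|---|
| 10 | 39.8% | 59.4% | 39.8% | 94.9% | 79.3% | 40.0% |
| 15 | 25.1% | 74.1% | 25.1% | 96.3% | 90.9% | 53.1% |
| 20 | 15.8% | 81.5% | 15.8% | 97.3% | 95.5% | 63.9% |
| 30 | 6.3% | 92.3% | 6.3% | 95.6% | 94.2% | 78.2% |
| 40 | 2.5% | 87.1% | 12.2% | 95.3% | 93.9% | 86.8% |
| 50 | 1.0% | 93.1% | 5.8% | 96.1% | 94.1% | 91.1% |
| 255 | 0.0% | 95.0% | 3.3% | 95.5% | 94.2% | 95.5% |

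Coverage does not rise smoothly because the data are discrete. At n = 40, for example, 39/40 gives limits of 92.5% to 100%, which also miss 91.2%. In every row most of the misses lie above the true value.

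**Step 4: what other intervals give when all are detected.** The bootstrap gives 100% to 100% in each case.
- 10/10: Wilson from 72.2%, Clopper-Pearson from 69.2%
- 20/20: Wilson from 83.9%, Clopper-Pearson from 83.2%
- 30/30: Wilson from 88.6%, Clopper-Pearson from 88.4%

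For n = 10 to 50 and true sensitivity 0.85, 0.912 or 0.95, Wilson coverage stays between 91% and 98%. Clopper-Pearson stays at 97% or above.

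**Step 5: whole cohort.** Sensitivity: bootstrap 87.7% to 94.6%, Wilson 87.3% to 94.2%. Specificity: bootstrap 48.0% to 58.0%, Wilson 48.0% to 57.9%. The choice makes no practical difference here.

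**The case against.** The best defence is that the problem is narrow and may never arise. A two-level split of 255 occluded patients averages about 127 per level, and three coronary territories average 85. Coverage at 0.912 is 93% at both sizes, and the chance of observing 100% is 0.04% or less. Subgroups may be combined, and a rule for sparse cells is the kind of detail a full protocol or analysis plan often holds.

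Much of this stands. The document does not show that any subgroup will be as small as 10 or 20 occluded patients. The 91.2% is expert rather than model performance, and at a true sensitivity of 0.85 there is no shortfall at n = 20. At the plan's 53% specificity, bootstrap coverage for specificity is 93% to 96% with as few as 5 to 50 patients, so the calculations do not require a change for that metric.

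The defence does not remove the point. Uneven splits are ordinary, particularly in ECG and comorbidity strata. The combining clause is discretionary and sets no minimum size. The interval method is stated for all metrics without exception, so the objection is to a stated choice and not to an omission. The collapse at n/n occurs under any ordinary non-parametric resampling of patients, whichever variant is used.

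**Conclusion.** The point holds for secondary subgroups with about 40 or fewer occluded patients. There the sensitivity interval can under-cover badly (59% at 10, 82% at 20 and 87% at 40 for a true sensitivity of 0.912), and sensitivity and NPV lose their error bars when no occlusion is missed. The shortfall worsens as true sensitivity rises. From about 50 occluded patients it is small: 91% to 94% over 0.85 to 0.95.

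Four stronger readings are not supported:
- A reader might infer that every metric collapses. Step 2 shows that specificity, PPV, accuracy and F1 keep their width.
- A reader might infer that the primary result is affected. With about 255 occluded patients it is not.
- A reader might infer that the forest plots are bound to be wrong. That depends on subgroup sizes the article does not give.
- A reader might infer that the smallest groups always show the tightest bars. That needs an estimate of exactly 100%; 9/10 gives about 70% to 100%, far wider than the cohort's 7 points.

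The coverage figures assume the percentile variant, treat the number of occluded patients in a subgroup as fixed, and use illustrative subgroup sizes. An analysis plan that is not shown may already contain a rule for such cells.

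**What to change.** In the subgroup forest plots, use Wilson or Clopper-Pearson 95% intervals for the simple proportions. This matters most for sensitivity and NPV; for specificity, PPV and accuracy it is mainly a matter of using one method throughout. Print the number detected and the number occluded beside each sensitivity estimate. The same intervals may be used for the whole cohort for consistency, where the results barely change. Keep the bootstrap for F1. Write the rule down before subgroup results are seen. The cost is a change of interval formula: no extra patients, data or procedures.

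### Culprit-territory subgroups are tested against an overall cohort that can include patients without a culprit, so every territory P value except that for sensitivity mixes territory with case mix

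*Protocol article*

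**What the plan says.** Table 2 of the Protocol article (AI-ECG TIMI model end points, item 1) lists the factors across which model performance is examined, the last being "4) culprit artery territory". Under Statistical analysis, Primary and secondary end points, "forest plots will evaluate demographic, electrocardiographic, and culprit artery subgroup model performance". The same paragraph sets one rule for each subgroup: "P* values will compare performance within a subgroup to the performance of the model on the overall patient population". It makes no exception for culprit territory. The only flexibility is that some subgroups may be merged, which leaves the comparator as it is.

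On who is in the overall population, Screening and eligibility criteria states: "Consecutive patients with a working diagnosis of ACS (both STEMI and non-STEMI) admitted for ICA as per standard practice will be included", and "Interventional cardiologists will enroll patients before the ICA procedure". No exclusion in Table 1 removes a patient in whom angiography then finds no culprit. Index procedures adds: "For patients without a culprit vessel requiring urgent revascularization, T2 and T3 time points will be skipped". Such patients keep the T1 ECG, which is the one used for the primary end point.

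Study outcomes lists accuracy, sensitivity, specificity, PPV, NPV and F1 as the performance measures. The article does not say which of them the subgroup P value uses.

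**The concern.** Age or sex groups together make up the whole cohort. Culprit territories do not: LAD, LCx and RCA groups together contain only patients with a culprit. The comparator can also hold patients without one, who cannot be TIMI 0-1 in a culprit artery and so enter only as reference-negatives. Two things follow.

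- **Specificity.** Within a territory the denominator is TIMI 2-3 culprits only. Overall it also includes no-culprit patients, whose ECGs may be easier to call negative.
- **Prevalence.** The share with active occlusion is higher among culprit patients than overall. PPV and NPV therefore differ even if specificity is the same everywhere.

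A reader of the forest plot would take P < .05 beside a territory as a weakness (or strength) of the model in that artery. Part or all of the difference may come from patients who belong to no artery. Testing each territory against its complement does not help, because the complement still holds the no-culprit patients.

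**Working it through.** **Plan's own figure.** Inputs from Sample size and interim analysis: specificity 53%, prevalence 40%, precision 5% (read as CI half-width), 95% CI, dropout 10%. Non-occluded patients needed: 1.96² × 0.53 × 0.47 / 0.05² = 382.8. Dividing by 0.60 gives 638 evaluable, and 638 / 0.90 gives 709. This matches the plan, so 638 is used below.

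**Assumptions not in the article.** No-culprit share of the cohort q; specificity in those patients s; territory shares 40/20/40 (LAD/LCx/RCA). All three territories are given the same specificity c, so there is no territory effect.

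**Sensitivity.** Every TIMI 0-1 patient has a culprit, so the expected value is 0.912 in culprit patients and 0.912 overall, whatever q and s are.

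**Specificity.** Overall specificity = [q·s + (0.60 − q)·c] / 0.60.

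- If 53% is the overall figure, q = 20%, s = 80%: c = (0.60 × 0.53 − 0.20 × 0.80) / 0.40 = 0.158 / 0.40 = 0.395 in every territory, against 0.530 overall.
- If 53% is the culprit-patient figure, same q and s: overall = (0.16 + 0.212) / 0.60 = 0.620, against 0.530 in every territory.

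**PPV and NPV with s = c = 53%, q = 20%.** Prevalence among culprit patients is 0.40 / 0.80 = 50%, against 40% overall.

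- PPV, culprit patients: 0.912 / (0.912 + 0.47) = 0.660. Overall: 0.3648 / (0.3648 + 0.282) = 0.564.
- NPV, culprit patients: 0.53 / (0.53 + 0.088) = 0.858. Overall: 0.318 / (0.318 + 0.0352) = 0.900.

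**Accuracy and F1 with c = 53%, s = 80%, q = 20%.** Accuracy is 0.721 in culprit patients against 0.737 overall, and F1 is 0.766 against 0.735.

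**Rejection rates for specificity.** 20,000 simulated trials, N = 638, two-sided 5%, two-sample z test of each territory against the overall cohort, treating the two as independent:

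| q | s | Culprit specificity | Overall specificity | LAD / LCx / RCA rejected | All three rejected |
|---|---|---|---|---|---|
| 20% | 80% | 39.5% | 53% | about 74 / 43 / 74% | about 16% |
| 20% | 80% | 53% | 62% | about 35 / 21 / 34% | 0.2% |
| 20% | 80% | 70% | 73.3% | about 5% each | 0% |
| 10% | 70% | 49.6% | 53% | about 3–5% | 0% |

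In the first row at least one territory is flagged in 99% of runs. Against the complement, the rates in that row are about 89% (LAD, RCA) and 55% (LCx). Against other culprit patients they are about 5% in every row.

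**A second form of the test.** Each territory is part of its own comparator, so treating the two as independent makes the test conservative. A version that allows for the overlap, with c = 53% and shares 45/35/20%, rejects for specificity in 65/51/28% (q = 20%, s = 80%) and 29/20/12% (q = 10%, s = 80%). For PPV with equal 53% specificity and q = 20% it rejects in 88/75/47%. For sensitivity it stays at 4–8%. With a culprit-only comparator all metrics tested return to about 4–7%.

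**The case against.** The strongest reply is that the plan asks a different question. It tests whether performance in a subgroup differs from overall performance. If specificity really is lower in culprit patients, that null is false and rejecting it is no error. That is formally right, and the rates above are not type I errors of the literal test. But the factor is labelled culprit artery territory, and a significant result on that row will be read as a statement about the artery. The literal test cannot support that reading.

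The size is also open to challenge, and that challenge stands. The article gives neither the no-culprit share nor the specificity in those patients. The 53% is an expert figure, not the model's, and the article itself calls it a likely underestimate. Milder inputs bring the rejection rate for specificity down to about 5%.

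The sentence about skipping T2 and T3 could also cover a patient whose culprit needs no urgent treatment, so it does not by itself prove that no-culprit patients are expected. Enrolment before angiography on a working diagnosis admits them on either reading.

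Three stronger readings are tempting but unsupported.

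- A reader might infer that all the territory P values are spoiled. Sensitivity is not affected.
- A reader might infer that the test is purely culprit versus no culprit. It mixes that contrast with any real territory difference.
- A reader might infer that all three territories will usually be flagged together. This happens in about 16% of runs in the first scenario tabulated and almost never in the other three.

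A fuller protocol or SAP may define how patients without a culprit are handled. The comparator rule, however, is stated in the article and is wrong for this factor as it stands.

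**Conclusion.** The point holds for specificity, PPV, NPV, accuracy and F1. The stated comparator can contain reference-negative patients that no territory can contain, so a territory P value may be small with no difference between territories. For PPV and NPV this needs only a no-culprit share above zero, because prevalence shifts. For specificity it also needs the model to perform differently in no-culprit patients.

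The size cannot be fixed from the article. In the scenarios tabulated, rejection for specificity runs from no visible excess over 5% to about 74% per territory. The most likely harm is a false flag on one or two territories. This is one of four subgroup factors within one secondary end point. It should be corrected before results are seen, but it does not touch the primary end point or the sample size.

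**What to change.** For the culprit-territory factor only, replace the comparison with the overall population by a comparison among patients with an identified culprit. This can be a heterogeneity test across LAD, LCx and RCA, or each territory against the other culprit patients. Compare sensitivity among TIMI 0-1 culprits and specificity among TIMI 2-3 culprits. Show patients without a culprit as a separate descriptive row in the forest plot.

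The cost is one sentence of analysis wording and a smaller comparator for these tests. No new data are needed, and the 709 patients and the primary analysis are unchanged.
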